## Appendix A (cont'd) Schedule of Assessments

---

|   |                                                                                                                                                                                                                                                                                                                                                                                                                             |
|---|-----------------------------------------------------------------------------------------------------------------------------------------------------------------------------------------------------------------------------------------------------------------------------------------------------------------------------------------------------------------------------------------------------------------------------|
| o | Systolic and diastolic blood pressure and pulse.                                                                                                                                                                                                                                                                                                                                                                            |
| p | Body weight.                                                                                                                                                                                                                                                                                                                                                                                                                |
| q | Complete blood count with differential (RBC count, Hgb, hematocrit, MCV, MCH, MCHC, leukocytes, neutrophils, basophils, eosinophils, monocytes, lymphocytes, reticulocytes, platelets, haptoglobin); coagulation panel (PT/INR).                                                                                                                                                                                            |
| r | Alanine transaminase, AST, gamma-glutamyl transpeptidase, lactate dehydrogenase, total/direct/indirect bilirubin, alkaline phosphatase, total protein, albumin, BUN/urea, creatinine, glucose, calcium, magnesium, phosphorus, sodium, potassium, chloride, bicarbonate, amylase, lipase, CK, CK-MB, troponins (only if CK-MB is abnormal after baseline), lactic acid, and calculation for CRCL.                           |
| s | HbA1c only for patients with Type 1 and 2 diabetes.                                                                                                                                                                                                                                                                                                                                                                         |
| t | Urine chemistry for protein, microalbumin, and creatinine. Urinalysis consisting of color and clarity, specific gravity, pH, protein, glucose, ketones, bilirubin, urobilinogen, blood, nitrite, and leukocyte esterase. Urine microscopic for WBC, WBC clumps, RBC, RBC clumps, epithelial cells, crystals, bacteria, yeast, mucous, and casts (see Appendix H for urine protein/creatinine calculations). |
| u | For patients showing viral load breakthrough, relapse, or partial response, a confirmatory sample must be obtained within 2 weeks.                                                                                                                                                                                                                                                                                          |
| v | Collected predose.                                                                                                                                                                                                                                                                                                                                                                                                          |
| w | Collected prior to Pegasys dose.                                                                                                                                                                                                                                                                                                                                                                                            |
| x | To be accompanied by symptom-directed physical examination as appropriate.                                                                                                                                                                                                                                                                                                                                                  |
| y | After informed consent, but prior to initiation of study medications, only SAEs caused by a protocol-mandated intervention will be collected (e.g., SAEs related to invasive procedures such as biopsies).                                                                                                                                                                                                                  |

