## **2.2 SECONDARY OBJECTIVES**

The secondary objectives for this study are as follows:

- To estimate the sustained virologic response 24 weeks after treatment (SVR-24) for the two experimental treatment groups
- To estimate the sustained virologic response 4 weeks after treatment (SVR-4) for the two experimental treatment groups
- To estimate the virological response over time (all visits) for the experimental treatment groups
- To estimate the proportion of patients who develop resistance to boceprevir and/or RO5024048
- To compare the safety and tolerability of the treatment groups

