## **4.2 METHOD OF TREATMENT ASSIGNMENT AND BLINDING**

Approximately 60 patients who qualify for the study will be enrolled. Patients will be randomized in a 1:1 ratio. Randomization will be centralized and stratified by HCV genotype (1a or 1b) and by IL28B genetic polymorphism (CC, CT, or TT).

The study is double-blind, and neither study staff, monitors or patients will know which treatment arm individuals have been randomized to.

The randomization list will not be provided to the study center and to the monitors. Patients who have previously been enrolled in Group C will be unblinded and offered mericitabine, in addition to the treatment they are receiving, for a maximum of 24 weeks.

An IMC and safety project team will be unblinded for routine aggregate safety reviews. For purposes of modeling and simulation, drug resistance monitoring, and PK analysis, select members will be unblinded. In order for the Sponsor to make recommendations or decisions regarding further development of the drug, selected members of the project team will have access to the blinding code for interim analyses.

In order to facilitate analysis of the biologic samples collected in this study, the treatment code will be released—according to procedures in place to ensure the integrity of the data—to the responsible analytical person when the samples have been received at the analytical site and are ready for assay. The result of the analysis must not be released with individual patient identification until the database is closed.

If unblinding is necessary for patient management (in the case of a SAE), the investigator will be able to break the treatment code by contacting the interactive voice response system (IVRS). Treatment codes should not be broken except in emergency situations. If the investigator wishes to know the identity of the study drug for any reason, he or she should contact the Medical Monitor directly. The investigator should document and provide an explanation for any premature unblinding (e.g., accidental unblinding, unblinding due to a SAE).

As per health authority reporting requirements, Roche will break the treatment code for all unexpected SAEs (see Section 5.7) that are considered by the investigator to be related to the study drug.

All other individuals directly involved in this study will remain blinded until all patients have completed all study assessments and the database is cleaned and closed.

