## Appendix A (cont'd)

### Schedule of Assessments

---

Ab = antibody; AE = adverse event; AFP = alpha-fetoprotein; AMA = antimitochondrial Ab; ANA = antinuclear Ab; ASMA = antismooth muscle Ab; AT = antitrypsin; CK = creatine kinase; CRCL = creatinine clearance; CT = computerized tomography; HAV = hepatitis A virus; HBsAg = hepatitis B surface antigen; HCV = hepatitis C virus; Hgb = hemoglobin; INR = International Normalized Ratio; Serum IP-10 = interferon gamma-induced protein 10kDa; MCH = mean corpuscular hemoglobin; MCHC = mean corpuscular hemoglobin concentration; MCV = mean corpuscular volume; MRI = magnetic resonance imaging; PD = pharmacodynamic; PK = pharmacokinetic; PT = prothrombin time; PW = Premature Withdrawal Visit; RCR = Roche Clinical Repository; SAE = serious adverse event; TSH = thyroid-stimulating hormone.

- a Assessments to be performed 4, 12, and 24 weeks after the last dose of study treatment in all patients who completed treatment. Patients who prematurely discontinue from the study will be assessed for safety and efficacy at 4, 12, *and* 24 weeks after the last dose of study treatment.
- b All patients who prematurely withdraw are recommended to complete the PW Visit as soon as possible after the last dose of study medication and proceed with treatment-free follow up.
- c Includes height and weight.
- d Repeat if any change in medical condition is noted since the screening examination.
- e Physical examination only.
- f Only for patients with pre-existing pulmonary disease or current respiratory symptoms.
- g All patients must have a liver biopsy or fibroscan assessment. Fibroscan must be completed within 12 calendar months of the first dose (an elasticity score of  $\geq 12.5$  kPa will be used to designate incomplete/transition to cirrhosis (i.e., "cirrhotic") a score of  $\geq 9.5$  kPa but  $< 12.5$  kPa will require a patient to undergo a liver biopsy to determine whether he/she is designated as "cirrhotic" or "non-cirrhotic").
- h Ultrasound within 6 months prior to randomization. If a patient has had a CT or MRI scan within the 6-month period that includes cuts of the entire liver, these assessments may be substituted for an ultrasound as the liver imaging procedure. Endoscopy within 2 years prior to randomization.

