## Appendix C

### Creatinine Clearance Calculation

#### **ESTIMATED CREATININE CLEARANCE ACCORDING TO COCKCROFT GAULT**

##### **CONVENTIONAL UNITS**

$$\text{Creatinine Clearance (mL/min)} = \frac{(140 - \text{age}) \times \text{Body Weight (kg)}}{72 \times \text{Serum Creatinine (mg/dL)}}$$

$$\text{Female CRCL} = \text{Male CRCL} \times 0.85$$

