| Unintentional weight loss                                                                   | NA                                                                                                                                                 | 5 – 9% loss in body weight from baseline                                                                                                    | 10 – 19% loss in body weight from baseline                                                                                                                                                              | ≥ 20% loss in body weight from baseline OR Aggressive intervention indicated [e.g., tube feeding or total parenteral nutrition (TPN)]                                  |
| INFECTION                                                                            |                                                                                                                                                    |                                                                                                                                             |                                                                                                                                                                                                         |                                                                                                                                                                        |
| Infection (any other than HIV infection)                                                    | Localized, no systemic antimicrobial treatment indicated AND Symptoms causing no or minimal interference with usual social & functional activities | Systemic antimicrobial treatment indicated OR Symptoms causing greater than minimal interference with usual social & functional activities  | Systemic antimicrobial treatment indicated AND Symptoms causing inability to perform usual social & functional activities OR Operative intervention (other than simple incision and drainage) indicated | Life-threatening consequences (e.g., septic shock)                                                                                                                     |

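### Body weight is not scheduled after Week 24, although creatinine clearance is still calculated from it and the arms differ only from then on

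*Protocol*

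**What the plan says.** In the Appendix A vital-signs row, footnote p (body weight) is attached at Weeks 4, 8, 12, 16, 20 and 24. The entries at Weeks 30, 36, 42 and 48, follow-up Weeks 4, 12 and 24, and PW carry no such mark. Footnote o defines the row as "Systolic and diastolic blood pressure and pulse". The screening examination "Includes height and weight" (footnote c), while the Day 1 and PW examinations are "Physical examination only" (footnote e).

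The chemistry row is marked at every visit through Week 48, at follow-up Weeks 4 and 12, and at PW. Footnote r closes its list of chemistry items with "lactic acid, and calculation for CRCL". Appendix C gives the method as "ESTIMATED CREATININE CLEARANCE ACCORDING TO COCKCROFT GAULT", with body weight in the numerator.

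Sections 3.1 and 4.1 give both arms the same four drugs to Week 24. Arm A then stops, and Arm B continues boceprevir and Pegasys/Copegus to Week 48. A secondary objective in Section 2.2 is "To compare the safety and tolerability of the treatment groups". Appendix I grades unintentional weight loss against baseline; Grade 3, for example, is "10 – 19% loss in body weight from baseline".

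**The concern.** The schedule asks for a calculation at visits where it does not collect one of the inputs. After screening, weight is scheduled only while the two arms receive identical treatment. Once the arms separate, weight change can be captured only if someone reports it as an adverse event, so its percentage grading has no regular measurement behind it.

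The later CRCL values have a use. Section 6.5 summarises abnormal laboratory findings by treatment group through the treatment-free follow-up. Section 1.2.1 describes glomerular changes in monkeys that reversed after dosing stopped. Appendix G has renal events followed, with calculated CRCL, until they settle or return to the starting level. If weight moves without being recorded, part of the apparent stability or recovery in CRCL comes from the input and not from the kidney. No later analysis can supply a weight that was never taken.

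**Working it through.** The plan gives no figure of its own on this point, so the check sets the two schedule rows against each other and then tests how sensitive the formula is.

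**Inputs.** Weight visits: screening and Weeks 4 to 24 (Appendix A, footnotes c and p). CRCL visits: all chemistry visits (footnote r). End of treatment: Week 24 in Arm A, Week 48 in Arm B (Section 4.1). Follow-up visits fall 4, 12 and 24 weeks after the last dose (Appendix A, footnote a).

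**Age of the latest scheduled weight.** For a patient who completes treatment, this is the study week of the visit minus 24.

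| Arm | Visit | Study week | CRCL due | Weight due | Age of last scheduled weight (weeks) |
|---|---|---|---|---|---|
| B | Week 30 | 30 | yes | no | 6 |
| B | Week 36 | 36 | yes | no | 12 |
| B | Week 42 | 42 | yes | no | 18 |
| B | Week 48 | 48 | yes | no | 24 |
| B | Follow-up 4 | 48 + 4 = 52 | yes | no | 28 |
| B | Follow-up 12 | 48 + 12 = 60 | yes | no | 36 |
| A | Follow-up 4 | 24 + 4 = 28 | yes | no | 4 |
| A | Follow-up 12 | 24 + 12 = 36 | yes | no | 12 |

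Follow-up Week 24 has vital signs but neither chemistry nor weight in either arm. PW has chemistry without weight. Among the visits after Week 24, weight is scheduled at none of the four treatment visits, none of the three follow-up visits, and not at PW.

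**Sensitivity of CRCL.** Appendix C: CRCL = (140 − age) × weight / (72 × serum creatinine), times 0.85 for women. Age, creatinine and the sex factor cancel in the ratio of the value computed with an old weight to the value computed with the current weight. If a fraction d has been lost since the last weighing, the ratio is 1 / (1 − d).

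| Assumed unrecorded loss | Ratio | CRCL overstated by |
|---|---|---|
| 2% | 1 / 0.98 = 1.020 | 2.0% |
| 5% | 1 / 0.95 = 1.053 | 5.3% |
| 10% | 1 / 0.90 = 1.111 | 11.1% |

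An unrecorded gain works the other way: with a gain of 5%, 1 / 1.05 = 0.952, so CRCL is understated by 4.8%. The documents state no expected weight change in either arm. All these percentages are assumptions chosen to show the range.

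**The case against.** The strongest defence is that the weight schedule follows RO5024048 dosing. That drug is given for at most 24 weeks in both arms. The CRCL stopping rules (Section 4.6.1.1 and Appendix F) act on that drug alone, and the CRCL monitoring band in Appendix G ends two weeks after it. For patients completing RO5024048 in Arms A and B, no CRCL rule operates beyond about Week 26, when the Week 24 weight is at most two weeks old. Later renal follow-up also has serum creatinine and, in Table H1, the urine protein/creatinine ratio to Week 60; neither uses weight. Weight is not a named outcome, no between-arm CRCL analysis is specified, and the study is exploratory with 30 patients per arm.

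Most of this stands, and it limits the reach of the point. It does not explain why CRCL stays on the schedule after the weights stop.

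Four stronger readings are tempting and not supported:

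- **Weight loss cannot be compared between arms.** Adverse events are still collected at the later visits and weight loss can be graded there; what is missing is systematic measurement.
- **Every later CRCL rests on an outdated weight.** The protocol does not say which weight enters the formula, and an unscheduled weight could be used.
- **Stopping decisions in Arms A and B are distorted after Week 24.** Patients in those arms are then off RO5024048.
- **The gap creates an artificial CRCL difference of a known size between arms.** That needs an assumed loss in Arm B and an assumed regain in Arm A, and the documents give neither.

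Two exceptions to the defence remain. Former Group C patients are to be "offered mericitabine, in addition to the treatment they are receiving, for a maximum of 24 weeks" (Section 4.2). Some could therefore be on RO5024048 after study Week 24, but their number and timing are not stated. A PW visit can also fall inside the RO5024048 window. There all study drugs have already been stopped, so the Appendix G monitoring band is what could be affected; for a withdrawal between Weeks 4 and 24 the last scheduled weight would be about four weeks old or less.

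**Conclusion.** The point holds as a gap between the schedule, footnote r and Appendix C. CRCL is required after Week 24 with no scheduled weight to go with it, the latest scheduled weight is 6 to 36 weeks old in Arm B and 4 to 12 weeks old in Arm A, and weight change is not measured systematically in the period when the arms differ. The resulting error in CRCL is in direct proportion to any unrecorded change: 2.0% to 11.1% too high for an assumed loss of 2% to 10%.

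For Arms A and B the effect is on the descriptive safety and renal-recovery data after Week 24. The renal rules tied to RO5024048 could be touched only for former Group C patients treated past study Week 24 or at a PW visit inside the drug's window. The primary endpoint and the sample size are unaffected. This is a modest weakness, worth correcting because the correction is cheap and the missing data cannot be recovered later.

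**What to change.** In Appendix A, attach footnote p to the vital-signs entries at Weeks 30, 36, 42 and 48, follow-up Weeks 4, 12 and 24, and PW. Add to footnote r or Appendix C that CRCL uses the weight taken at that visit where one is scheduled, and otherwise the most recent recorded weight. The second clause is needed because Day 1, Week 1 and Week 2 also have chemistry without a scheduled weight; a plain same-visit rule could not be met there. Together these changes reconcile the schedule, footnote r and Appendix C.

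No dose, threshold or stopping rule changes. The cost is one extra eCRF field and a weighing at visits where blood pressure and pulse are already taken. No visit is added.

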## **Appendix B**

### **Liver Biopsy Scores**

All patients must have a liver biopsy consistent with CHC. Patients not yet designated as having cirrhosis or incomplete/transition to cirrhosis must have had a liver biopsy within 24 calendar months prior to the first dose. For patients with cirrhosis or incomplete/transition to cirrhosis have, there is no time frame for the biopsy. The biopsies must be scored using one of the scales described below.

Transition to cirrhosis will be classified as a Metavir score of 3, a Batts and Ludwig score of 3, a Scheuer score of 3, or an Ishak Modified HAI score of 4 with nodules or > 3 bridges or a score of 5.

Patients with transition to or incomplete cirrhosis are to be classified as cirrhotic.

#### **METAVIR FIBROSIS SCORE**

- 0 No fibrosis
- 1 Stellate enlargement of portal tract but without septa formation
- 2 Enlargement of portal tract with rare septa formation
- 3 Numerous septa without cirrhosis
- 4 Cirrhosis

#### **BATTS and LUDWIG**

- 0 No fibrosis; normal connective tissue
- 1 Portal fibrosis; fibrous portal expansion
- 2 Periportal fibrosis; periportal or rare portal–portal septa
- 3 Septal fibrosis; fibrous septa with architectural distortion; no obvious cirrhosis
- 4 Cirrhosis

#### **THE SCHEUER SYSTEM**

- 0 None
- 1 Enlarged, fibrotic portal tracts
- 2 Periportal or portal-portal septa but intact architecture
- 3 Fibrosis with architectural distortion but no obvious cirrhosis
- 4 Probable or definite cirrhosis

## **Appendix B**

### **Liver Biopsy Scores (cont.)**

#### **ISHAK MODIFIED HAI FIBROSIS SCORE**

- 0 No fibrosis
- 1 Fibrous expansion of some portal areas, with or without short fibrous septa
- 2 Fibrous expansion of most portal areas, with or without short fibrous septa
- 3 Fibrous expansion of most portal areas, with occasional portal to portal bridging
- 4 Fibrous expansion of portal areas, with marked bridging (portal to portal) as well as portal to central
- 5 Marked bridging (portal to portal and/or portal to central) with occasional nodules (incomplete cirrhosis)
- 6 Cirrhosis, probable or definite

## Appendix C

### Creatinine Clearance Calculation

#### **ESTIMATED CREATININE CLEARANCE ACCORDING TO COCKCROFT GAULT**

##### **CONVENTIONAL UNITS**

$$\text{Creatinine Clearance (mL/min)} = \frac{(140 - \text{age}) \times \text{Body Weight (kg)}}{72 \times \text{Serum Creatinine (mg/dL)}}$$

$$\text{Female CRCL} = \text{Male CRCL} \times 0.85$$

